## Abstract

**Background:**

Advancements in wearable sensors have caused a resurgence in their use, particularly because their miniaturization offers ambulatory advantages while performing continuous vital sign monitoring. Digital alerts can be generated following early recognition of clinical deterioration through breaches of set parameter thresholds, permitting earlier intervention. However, a systematic real-world evaluation of these alerting systems has yet to be conducted, and their efficacy remains unknown.

**Objective:**

The aim of this study is to implement wearable sensors and digital alerting systems in acute general wards to evaluate the resultant clinical outcomes.

**Methods:**

Participants on acute general wards will be screened and recruited into a trial with a pre-post implementation design. In the preimplementation phase, the SensiumVitals monitoring system, which continuously measures temperature, heart, and respiratory rates, will be used for monitoring alongside usual care. In the postimplementation phase, alerts will be generated from the SensiumVitals system when pre-established thresholds for vital parameters have been crossed, requiring acknowledgement from health care staff; subsequent clinical outcomes will be analyzed.

**Results:**

Enrolment is currently underway, having started in September 2017, and is anticipated to end shortly. Data analysis is expected to be completed in 2021.

**Conclusions:**

This study will offer insight into the implementation of digital health technologies within a health care trust and aims to describe the effectiveness of wearable sensors for ambulatory continuous monitoring and digital alerts on clinical outcomes in acute general ward settings.

**Trial Registration:**

ClinicalTrials.gov NCT04638738; https://clinicaltrials.gov/ct2/show/NCT04638738.

**International Registered Report Identifier (IRRID):**

DERR1-10.2196/26240

## Introduction

Vital signs and their trends are crucial in recognizing clinical deterioration, with changes often occurring several hours prior to an adverse event [1-7]. Consequently, monitoring of these physiological parameters forms a fundamental component of providing effective clinical care. Despite this, patient deterioration can go undetected, resulting in adverse clinical outcomes such as late referrals to intensive care units, increased morbidity, and mortality [8-13].

Routinely measured vital signs include heart rate, respiratory rate, temperature, blood pressure, oxygen saturation (and supplemental oxygen), and level of consciousness. Individuals admitted to nonintensive (general) hospital wards undergo intermittent monitoring of these vital signs. A “track and trigger” early warning score (EWS) is recommended in the United Kingdom; the National Early Warning Score 2 (NEWS2) provides guidance on escalation protocols and the monitoring frequency of vital signs. Each vital parameter is individually scored according to severity and combined for a total NEWS score. Most frequently, observations are performed every 4-6 hours unless the patient is acutely unwell [14].

EWSs are predicated around the idea that hospital inpatients at high risk of deterioration are identified early through prodromal vital parameter alterations (eg, elevated respiratory rate), enabling early intervention [15]. Since their implementation, EWSs have shown good predictive value for deterioration and have improved clinical outcomes [16]. However, their intermittent nature is a critical limitation that enables acute deterioration between measurements to be easily missed [16].

Wearable sensors and digital alerting mechanisms offer a potential solution to this issue. Continuous monitoring through novel wearable sensors provides near real-time monitoring of vital signs without hindering ambulation. It is theorized that continuous monitoring will enable earlier detection of deterioration through a culmination of additional data points and reduced reliance on availability of medical personnel for performing observations [17]. Alerts are subsequently generated, informing health care professionals when pre-established thresholds for vital parameters, often tailorable, are breached. However, the evidence supporting the use of wearable sensors outside of intensive care settings remains mixed and limited [18,19]. The heterogeneity of study designs and complexity of interventions used, however, limit meaningful conclusions.

Here, we describe the design of our trial, in which we implement wearable sensors and digital alerting systems in acute general wards in a National Health Service hospital; we also describe the implementation strategy and the evaluation of the resultant clinical outcomes (eg, length of stay, mortality, need for intensive care).

## Methods

### Study Design

This is a single-center, pre-post design in which digital alerting systems are implemented on acute wards. The preimplementation phase dated from September 2017 to August 2019, and the postimplementation phase is currently underway.

The preimplementation phase involved using the SensiumVitals system in accordance with usual care. However, health care staff were not able to view the continuous vital sign monitoring data or the digital alerts generated for abnormal parameters. Usual care, in our institution, involves intermittent monitoring of vital signs in accordance with NEWS2.

In the postimplementation phase, alerting systems following recognition of abnormal parameters will be included. These alerts will be transmitted to mobile devices and central monitoring hubs, with alert acknowledgement required from health care staff.

All participants provided informed consent. Ethical approval for this study has been granted by a Research Ethics Committee (Integrated Research Application System: 222979). The trial will be performed in accordance with Good Clinical Practice guidelines and the Declaration of Helsinki. Patient data will be anonymized to ensure privacy. Storage and handling of personal data will comply with the General Data Protection Regulation.

### Intervention Protocol for Alerts

All alerts will be viewed by dedicated trained nursing staff covering the wards. Alerts will be generated when measured vital signs exceed pre-established thresholds for 10 consecutive minutes. These thresholds can be individually tailored but are initially programmed to trigger if the patient’s temperature exceeds 38.1 ºC, respiratory rate is over 25 breaths per minute, and heart rate is over 131 beats per minute, in accordance with NEWS2 cutoffs [14]. All incoming alerts are deemed to be of potential clinical relevance, and potential outcomes include but are not limited to reviewing the individual, repeating observations, increased frequency of monitoring, and escalation to a responsible physician.

### Stakeholder Engagement

Several stakeholders will continue to be engaged during the establishment of the project; permission from the Estates and Information Technology departments has been obtained. This permission ensured that bridges were installed by the hospital Estates department, enabling adherence with local policies. Monitoring software has been integrated with the hospital admissions data system, enabling consenting participants to be easily added to the system. Data will be stored and retained on hospital networks, alleviating data security concerns. Senior clinicians have been informed of the project through engagement meetings to drive recruitment and elucidate the aims of the study. Nursing staff have been trained directly to use the system; ad hoc refreshers will be available throughout the duration of the study.

### Eligibility Criteria

Adults (aged over 18 years) admitted to general wards who are able to understand the participant information sheet are eligible for inclusion. Individuals with cardiac implantable electronic devices, who experience a skin reaction to the wearable sensor or its components, who have an open chest wound, or who withdraw consent will be excluded.

Recruitment will be aided by the responsible clinical team, who will deem individuals suitable to participate.

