### Data Collection

After enrolment, data will be routinely collected by two research nurses and a clinical fellow. Outcomes will be obtained from case note review, SensiumVitals data, and electronic health records, enabling prospective data collection.

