### Outcome Measures

Outcome measures will include hospital length of stay; critical NEWS (defined as 7 or over); number of admissions to intensive care; mortality; sepsis events; and time to antibiotics.

To understand the acceptability and usability of the SensiumVitals system by participants and health care staff, mixed methods analysis (semistructured interviews and questionnaires) will be undertaken in the postimplementation phase. For participants, these interviews and questionnaires will be administered 24 hours after the SensiumVitals sensor has been applied, enabling familiarity with the sensor and maximizing of data capture before potential hospital discharge. Due to the nature of the shift patterns, a set time point has not been chosen for health care staff; however, the studies will only be conducted once familiarity with the system has been established. All key stakeholders will also be invited to take part in semistructured interviews to determine barriers and facilitators to implementing wearable sensors and alerting mechanisms within the hospital.

The questionnaires consist of 5-point Likert scale responses (strongly disagree to strongly agree), with elements adapted from the validated System Usability Scale [20].

Face-to-face interviews will be conducted by the lead researcher (FI) using a predetermined topic guide. Data collection will be an iterative process; emerging recurring concepts were incorporated into the interview guide for further exploration with remaining participants. Interviews will be recorded, anonymized, transcribed, and entered into NVivo 12 (QSR International) for analysis.

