### Data Monitoring

Overall, there is a low level of concern for patient safety with the SensiumVitals sensor, given previous use [22]. Furthermore, participants are at very low risk for adverse events; should any occur, they will be logged systematically and reported to ClinicalTrials.gov. Adverse events not related to the sensor will be reported to the responsible clinical team.

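### The eligibility rule excludes people for two on-study events, skin reaction to the sensor and withdrawal of consent; this can flatter acceptability and, under conditions, distort the phase comparison

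*Protocol article*

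**What the plan says.** The Eligibility Criteria section admits adults on general wards who can understand the information sheet. It then lists the exclusions in one sentence: a cardiac implantable electronic device, followed by individuals "who experience a skin reaction to the wearable sensor or its components, who have an open chest wound, or who withdraw consent will be excluded".

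Other sections that bear on this:

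- **Study Design:** "All participants provided informed consent". The sensor is worn in both phases: "The preimplementation phase involved using the SensiumVitals system in accordance with usual care", with staff unable to see the data or alerts. The change between phases is that "In the postimplementation phase, alerting systems following recognition of abnormal parameters will be included".
- **Data Collection:** "Outcomes will be obtained from case note review, SensiumVitals data, and electronic health records, enabling prospective data collection".
- **Outcome Measures:** acceptability and usability are studied in the postimplementation phase. For participants, "these interviews and questionnaires will be administered 24 hours after the SensiumVitals sensor has been applied".
- **Statistical Analysis:** propensity score matching addresses differences in baseline demographics between the phases.
- **Data Monitoring:** "participants are at very low risk for adverse events; should any occur, they will be logged systematically and reported to ClinicalTrials.gov".

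**The concern.** The exclusion sentence mixes two kinds of criterion. An implantable device and an open chest wound can be established before anyone is enrolled. Withdrawal cannot, and a reaction to this sensor ordinarily cannot either. A person who meets one of these two criteria is normally already a participant wearing the patch. Excluding that person selects the study group on a post-enrolment event.

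Three results could be touched:

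- **Acceptability.** People who react or withdraw within the first 24 hours are plausibly the least content with the patch. If they are out before the questionnaire, the remaining answers are too favourable. This needs no difference between the phases.
- **Phase comparison.** The groups compared would no longer be everyone enrolled in each phase. Matching on baseline demographics does not repair selection that happens later.
- **Skin reactions as adverse events.** The same event is both something to log and a ground for exclusion. The article does not say how such a participant is counted.

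**Working it through.** **The plan's own figures.** The article gives no rate of skin reaction, withdrawal or exclusion, so there is no figure to reproduce on this point. The target is at least 600 participants, about 300 per phase, with no stated allowance for exclusions. If 5% or 10% were removed, 600 × 0.95 = 570 or 600 × 0.90 = 540 would remain. All rates below are assumptions chosen to show a range.

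**Phase comparison, no true effect.** Let p be the true event risk in each phase, e the share excluded, k the risk in the excluded divided by the risk in the retained, and q the risk seen in the retained.

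- p = (1 − e)q + e·k·q, so q = p / (1 − e + e·k).
- Spurious risk ratio (post/pre) = (1 − e_pre + e_pre·k) / (1 − e_post + e_post·k). It does not depend on p.

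| Excluded, pre v post | k = 0.5 | k = 1 | k = 2 |
|---|---|---|---|
| 5% v 5% | 1.00 | 1.00 | 1.00 |
| 10% v 10% | 1.00 | 1.00 | 1.00 |
| 5% v 10% | 0.975/0.950 = 1.026 | 1.00 | 1.05/1.10 = 0.955 |
| 5% v 15% | 0.975/0.925 = 1.054 | 1.00 | 1.05/1.15 = 0.913 |

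At p = 10%, the 5% v 15% row gives:

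- k = 2: 0.10/1.15 − 0.10/1.05 = 0.0870 − 0.0952, about −0.8 percentage points.
- k = 0.5: 0.10/0.925 − 0.10/0.975 = 0.1081 − 0.1026, about +0.6 points.

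So a bias needs both unequal exclusion and a link with outcome, and its direction depends on whether those excluded are at higher or lower risk.

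**Acceptability, post phase only.** Let A_r be the share agreeing among those assessed and A_e the share who would have agreed among those lost before assessment.

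- Agreement in all = (1 − e)A_r + e·A_e.
- Overstatement = e(A_r − A_e).
- Smallest case assumed: e = 2%, A_r = 80%, A_e = 50%. 0.02 × 0.30 = 0.6 points.
- Middle case: e = 10%, A_r = 80%, A_e = 20%. 0.10 × 0.60 = 6 points.
- Largest case: e = 15%, A_r = 90%, A_e = 0%. 0.15 × 0.90 = 13.5 points.

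**Adverse events.** Set side by side, Data Monitoring requires any adverse event to be logged and reported and exempts nobody, while Eligibility Criteria excludes a person for one such event. Neither section says whether that person stays in the numerator and the denominator of a skin-reaction rate.

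**The case against.** The strongest reply is that the article never says excluded participants are dropped from the analysis. The sentence sits under eligibility, the Statistical Analysis section has no such rule, and analysis sets are commonly left to the full protocol or analysis plan, which are not shown. A skin reaction could also mean a known earlier reaction to the components, which can be screened at baseline. Part of this stands: the lack of an analysis-set definition in an article is not the finding, and the earlier-reaction reading is possible. But the article does state a rule of exclusion, nothing in it limits that rule to taking the sensor off, and withdrawal of consent has no baseline reading.

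Two stronger readings are tempting, and the documents do not support them.

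- **That the rule does bias the phase comparison, possibly by a lot.** Suppose the true risk is 10% and only post-phase patients leave, with risk 25%. Then (0.10 − 0.05 × 0.25)/0.95 = 9.2% and (0.10 − 0.10 × 0.25)/0.90 = 8.3%, apparent risk ratios of 0.92 and 0.83. This is a worst case. The exclusion rule is not confined to one phase, and the same sensor is worn in both, so reactions to it should largely cancel. The assumed risk in leavers is 2.7 to 3.0 times that in the retained (0.25/0.0921 and 0.25/0.0833), with no source. Withdrawals might differ, since only post-phase patients meet alert-driven reviews and the phases cover different periods, but the article gives no evidence on this.
- **That skin reactions vanish from the safety record.** Data Monitoring requires them to be logged, and a reaction must be observed before it can lead to exclusion. What remains is an unstated numerator and denominator.

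Two further points are fair. Ceasing to use a participant's data after withdrawal can be legitimate. And the preimplementation phase had closed in August 2019, so rewording cannot change who was enrolled. Analysis, however, was still ahead, so the analysis set could still be fixed.

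**Conclusion.** The point holds in a limited form. Two on-study events are written as exclusion criteria, and following the rule as written would select the analysed group after enrolment.

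- **Acceptability** is the strongest part. The direction of the error is plausible without any difference between phases. The size is unknown: 0.6 to 13.5 points if 2% to 15% are lost before assessment, with agreement of 80% to 90% in those retained and 0% to 50% in those lost.
- **Phase comparison:** bias is possible but not shown. It is nil if exclusions are alike in both phases, and stays within a risk ratio of about 0.91 to 1.05 for 5% v 15% excluded at half to twice the risk.
- **Safety:** only a need to reconcile two sections.

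Because the exclusion rate is not given, this should be corrected before analysis but ranks below a must-fix.

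**What to change.** 1. In Eligibility Criteria, keep only conditions known before enrolment. If an earlier reaction to the components was meant, say so. For the analysis, class an on-study skin reaction or sensor removal as sensor discontinuation. The clinical handling of a reaction is not at issue here.
2. Analyse every participant with a sensor applied, in the phase of enrolment, using outcomes from the case notes and electronic records. After withdrawal of consent, keep data up to that point as consent allows.
3. State in Data Monitoring that skin reactions leading to removal count as adverse events, with all sensors applied as the denominator.
4. Report skin reactions, early removals and withdrawals by phase over all sensors applied. Count early removals in the acceptability denominator, and offer the assessment to those who stop wearing the sensor early and remain in consent.

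The cost is mainly wording and a defined analysis set. Records are already a planned data source, and outcomes such as length of stay, intensive care admission and mortality do not depend on continued wear. The downside is slight dilution of any effect by participants who wore the sensor only briefly.

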### Data Collection

After enrolment, data will be routinely collected by two research nurses and a clinical fellow. Outcomes will be obtained from case note review, SensiumVitals data, and electronic health records, enabling prospective data collection.

### Outcome Measures

Outcome measures will include hospital length of stay; critical NEWS (defined as 7 or over); number of admissions to intensive care; mortality; sepsis events; and time to antibiotics.

To understand the acceptability and usability of the SensiumVitals system by participants and health care staff, mixed methods analysis (semistructured interviews and questionnaires) will be undertaken in the postimplementation phase. For participants, these interviews and questionnaires will be administered 24 hours after the SensiumVitals sensor has been applied, enabling familiarity with the sensor and maximizing of data capture before potential hospital discharge. Due to the nature of the shift patterns, a set time point has not been chosen for health care staff; however, the studies will only be conducted once familiarity with the system has been established. All key stakeholders will also be invited to take part in semistructured interviews to determine barriers and facilitators to implementing wearable sensors and alerting mechanisms within the hospital.

The questionnaires consist of 5-point Likert scale responses (strongly disagree to strongly agree), with elements adapted from the validated System Usability Scale [20].

Face-to-face interviews will be conducted by the lead researcher (FI) using a predetermined topic guide. Data collection will be an iterative process; emerging recurring concepts were incorporated into the interview guide for further exploration with remaining participants. Interviews will be recorded, anonymized, transcribed, and entered into NVivo 12 (QSR International) for analysis.

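### Recorded critical NEWS can rise in the postimplementation phase through detection alone, and the planned comparison does not correct for it

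*Protocol article*

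**What the plan says.** All references are to the protocol article.

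- **Outcome.** Outcome Measures includes "critical NEWS (defined as 7 or over").
- **Data sources.** Data Collection says "Outcomes will be obtained from case note review, SensiumVitals data, and electronic health records", without assigning a source to each outcome.
- **What the sensor covers.** The Abstract (Methods) and the Discussion give temperature, heart rate and respiratory rate. The Introduction adds blood pressure, oxygen saturation with supplemental oxygen, and consciousness to the routinely measured signs, and says that each parameter is scored towards the NEWS total.
- **Usual care.** Under the Introduction, "Most frequently, observations are performed every 4-6 hours unless the patient is acutely unwell". Study Design says that usual care follows NEWS2.
- **Pre phase.** The sensor is worn, but "health care staff were not able to view the continuous vital sign monitoring data or the digital alerts generated for abnormal parameters" (Study Design).
- **Post phase.** Alerts go to mobile devices and monitoring hubs and must be acknowledged. Intervention Protocol for Alerts gives the possible responses as including "reviewing the individual, repeating observations, increased frequency of monitoring, and escalation to a responsible physician".
- **Analysis.** Statistical Analysis names chi-square or Fisher tests for nominal data, and propensity score matching for differences in baseline demographics between phases.

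**The concern.** A score of 7 or over enters the data only if someone takes a full set of observations while the patient is that unwell. In the post phase the intervention itself can add sets, and it adds them when vital signs are abnormal, which is when a high score is most likely. In the pre phase no such prompt exists. The outcome may therefore be measured more intensively in one phase than in the other, as a consequence of what is being evaluated.

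The article describes the mechanism itself when it says of early warning scores that "their intermittent nature is a critical limitation that enables acute deterioration between measurements to be easily missed". An intervention meant to close that gap will, if it works as intended, also uncover scores that usual care would not have recorded.

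Matching on baseline characteristics cannot remove a difference in observation intensity that arises after enrolment. The limitations in the Discussion name longitudinal change in care delivery and the lack of causal inference. Differential detection is a separate problem: it would remain with perfectly comparable patients and no time trend. At stake is whether a rise in critical NEWS is read as harm, or an unchanged count as no benefit.

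**Working it through.** **The plan's own figure.** The minimum of 600 (about 300 per phase) cannot be reproduced. Power Calculations gives no alpha, power, effect size or event rate, and says that a formal calculation was not possible. The figure lies inside the 325-625 range cited for time to antibiotics. It is used below only as 300 per phase.

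**Inputs from the article.** Routine interval T = 4 or 6 h (Introduction); n = 300 per phase (Power Calculations).

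**Assumptions.** Episode length D = 1, 2 or 4 h. Alerts lead to a set that records a share s = 0.25 or 0.5 of the episodes routine sets would miss. In the table, 20% of patients in each phase truly have one episode. Alpha is 0.05 two-sided. There is no true difference between phases.

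**Formulas.**
- Pre-phase capture: a = min(1, D/T).
- Post-phase capture: b = a + (1 - a) × s.
- Recorded post/pre ratio: b/a, which does not depend on the true incidence.
- True reduction that detection would cancel: 1 - a/b.
- Chance of a significant false increase: normal approximation for two proportions, 300 per phase.

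Example: D = 1, T = 6, s = 0.5 gives a = 1/6 = 0.167, b = 0.167 + 0.833 × 0.5 = 0.583, and ratio 0.583/0.167 = 3.5.

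| D (h) | T (h) | s | Recorded pre v post | Ratio | Chance of false increase | Reduction cancelled |
|---|---|---|---|---|---|---|
| 1 | 6 | 0.5 | 3.3% v 11.7% | 3.5 | 0.97 | 71% |
| 2 | 6 | 0.5 | 6.7% v 13.3% | 2.0 | 0.78 | 50% |
| 1 | 4 | 0.25 | 5.0% v 8.8% | 1.75 | 0.44 | 43% |
| 2 | 4 | 0.25 | 10.0% v 12.5% | 1.25 | 0.16 | 20% |
| 4 | 6 | 0.25 | 13.3% v 15.0% | 1.13 | 0.08 | 11% |
| 4 | 4 | either | 20% v 20% | 1.0 | 0.025 (upper tail only) | 0% |

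**Sensitivity to capture.** Take a 10% true incidence (30 of 300 per phase) and 2-hour episodes, with z = difference / √(2p(1 - p)/300) and p the pooled proportion.

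- Full capture (s = 1): 6 h interval, 10 v 30 patients, P = 0.001; 4 h interval, 15 v 30, P = 0.020.
- Half capture (s = 0.5): 6 h interval, 10 v 20, z = 0.0333/0.0178 = 1.87, P about 0.06; 4 h interval, 15 v 22.5 expected, z = 0.025/0.0198 = 1.26, P about 0.21.

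The ratio therefore depends heavily on D and s, and the article gives neither.

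**The case against.** Several points on the other side stand, and they limit the claim.

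- **A reader might infer that the post phase will record more events.** The article does not support that. Repeat observations and closer monitoring are possible responses to an alert, not required ones. Episodes at least as long as the routine interval are caught in both phases. True prevention could lower the count.
- **Pre-phase capture may be better than D/T.** The 4-6 hour interval carries the exception for acutely unwell patients, and NEWS2 guides monitoring frequency. Patients already recognised as unwell may be observed more often in both phases.
- **Alerts will not catch everything.** The default triggers use three vital signs sustained for 10 minutes. A high score driven by blood pressure, oxygen or consciousness may trigger none.
- **A reader might infer a statistically significant false signal of harm.** In the 10% incidence, 2-hour example, P values of 0.001 to 0.02 need full alert capture. At half capture they are about 0.06 and 0.21.
- **A reader might conclude that a fall is uninterpretable too.** It is not, on this ground: the bias inflates the post-phase count, so a fall would appear in spite of it.
- **A reader might extend the point to sepsis events.** Outcome Measures only lists "mortality; sepsis events; and time to antibiotics", and nothing ties sepsis labelling to observation frequency. A similar effect is plausible, but it is an inference and not part of this finding.

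The Discussion also disclaims cause and effect, and mortality is not counted from NEWS. A fuller analysis plan, not shown, might deal with the issue. None of this equalises how critical NEWS is ascertained in the comparison the article describes.

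**Conclusion.** The point holds for critical NEWS in a limited form: the recorded count can rise in the post phase through detection alone, and nothing in the article corrects for this. The direction of the detection effect follows from the design, but its size is unknown.

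Under the working assumptions (episodes of 1 to 4 h, routine sets every 4 or 6 h, alerts catching 25% to 50% of otherwise missed episodes, no true change) the recorded ratio lies between 1.0 and 3.5. Detection could then cancel a true reduction of anything from 0% to 71%. With 300 per phase and 20% true incidence, the chance of a significant false increase runs from about 0.025 to 0.97.

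A rise or a null result is therefore ambiguous. A fall is conservative with respect to this bias, though still open to the time trends that the article acknowledges.

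**What to change.** 1. **Main comparison.** Count critical NEWS on one common grid of routine scheduled observations in both phases. For example, take the set nearest each scheduled time in fixed windows from sensor application, chosen by time alone. Do not exclude sets because they follow an alert acknowledgement. Acknowledgements exist only in the post phase, so that rule would remove sets taken during abnormal physiology from one phase and bias the result the other way.
2. **Sensitivity analysis.** Repeat the comparison with all observation sets.
3. **Observation intensity.** Report observation sets per patient-day by phase beside the result.
4. **Sensor-based measure.** Add a deterioration measure computed identically in both phases from the stored sensor data. The sensor was worn in both, so this does not depend on staff observations.
5. **Conclusion.** State that an all-sets comparison of critical NEWS is detection-dependent and is not, on its own, evidence of harm or of no effect.

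The cost is analysis wording and time-stamp filtering of existing records; no further participants are needed, and the article places completion of the analysis in the future. The downside is that genuine critical scores found only by unscheduled checks, possibly a substantial share, leave the main count and appear only in the sensitivity analysis.
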